### Participant timeline

Screening (week −2) → Baseline (week 0) → Follow-up visits at weeks 2, 4, 6, 8, 10, 12, 16, 20, and 24.

### Sample size

A total of 122 participants (61 per group) will provide 90% power to detect a 20% absolute difference in mean percentage wound area reduction (PWAR) at week 12 (65% in SOC + COMS versus 45% in SOC alone), assuming a standard deviation of 33%, a two-sided alpha of 0.05, and 5% attrition to account for potential loss to follow-up or drop-out [26, 27]. Sample-size calculations were performed using R (power.t.test). The assumptions were based on prior COMS pilot data and published SOC outcomes [21], where the mean wound area reduction with the COMS device was 70% (SD = 33%), and by two studies on SOC in chronic wounds [26, 27], where the mean reduction was approximately 45%. These data support the assumption of a 20% treatment effect in favor of COMS when added to standard care.

### Recruitment

Recruitment will occur consecutively at each site through outpatient wound care services and physician referrals. Sites will maintain a screening and enrollment log to track reasons for screening failures and randomization/intervention failures. Recruitment progress will be reviewed bi-weekly by the coordinating center.

### Assignment of interventions: allocation

Eligible participants will be randomized 1:1 to either SOC + COMS or SOC alone. The randomization sequence will be computer-generated by the study statistician using permuted blocks of variable sizes, stratified by site to maintain balance and minimize selection bias. Sequence generation will be performed using R with seed control and documented in a password-protected file accessible only to the statistician.

### Concealment mechanism

Allocation concealment will be ensured through the REDCap electronic data capture system, which automatically assigns treatment groups upon participant enrolment and eligibility criteria successful verification. The allocation sequence will remain concealed from site investigators until the system confirms randomization. No paper-based envelopes will be used.

### Implementation

The study statistician will generate the sequence; site investigators will enroll eligible participants; and REDCap will assign participants to groups automatically. This workflow maintains strict allocation concealment and traceability.

## Assignment of interventions: blinding

### Who will be blinded?

Due to the visible nature of COMS treatment, participant and clinician blinding is not feasible.

However, blinding will be maintained for outcome assessors, data analysts, and the steering committee. Wound images will be coded using participant’s unique identification numbers, and blinded assessors will review them centrally without knowledge of treatment arm or site. Statistical analyses will be conducted using masked treatment codes until database lock.

### Procedure for unblinding if needed

Unblinding will occur only if knowledge of allocation is essential for participant safety. The principal investigator may request unblinding via REDCap; the system will log all actions automatically. Outcome assessors will remain blinded whenever possible.

## Data collection and management

### Plans for assessment and collection of outcomes

Data will be recorded in REDCap, ensuring audit trails, role-based access, and secure encrypted storage. Ulcer size will be measured using standardized digital planimetry (ImitoWound), with calibration rulers and consistent lighting. Pain will be assessed via VAS; QoL via Wound-QoL questionnaire. Baseline variables (comorbidities, medications, ulcer history) will be collected through structured case report forms. Comorbidities collected include diabetes status and HbA1c, peripheral arterial disease, cardiovascular disease, hypertension, obesity (BMI), renal insufficiency, smoking status, and any condition associated with immunosuppression, as these are known to influence ulcer healing trajectories. Quality control checks will be implemented remotely after the inclusion of every 25 participants by an independent monitoring entity to identify and resolve discrepancies.

### Plans to promote participant retention and complete follow-up

Retention strategies include reminder calls for visits, flexible scheduling, and travel reimbursement (as permitted by local ethics). Participants who withdrew early will be invited for final data collection, and missing data will be minimized through prompt monitoring queries. Outcome data will be collected for all participants who discontinue intervention but consent to continued observation.

### Data management

Data entry will be performed by site staff and monitored remotely. Range checks and automated validation rules will be implemented in REDCap. All personal data will be pseudonymized using unique identifiers. The sponsor’s data management team will review cumulative data quality quarterly, and discrepancies will be resolved via Note-to-File/Deviation forms.

### Confidentiality

All participant data will comply with the GDPR and local data protection laws. Pseudonymized data will be stored on secure institutional servers; re-identification keys will remain locked separately at each site. Only authorized personnel will access identifiable data. Records will be retained for 20 years post-study completion in compliance with ISO 14155:2020. The NAZARÉ trial has received formal approval from the Geneva Ethics Commission (reference number 2024-D0096) and is registered at ClinicalTrials.gov (NCT06528873). All study procedures will comply with the Declaration of Helsinki (2013), ISO 14155:2020 for Good Clinical Practice in medical device investigations, and all applicable national and European regulations.

### Statistical methods

#### Statistical methods for primary and secondary outcomes

The primary endpoint (PWAR at week 12) will be analyzed using analysis of covariance (ANCOVA) adjusting for baseline ulcer area, ulcer type, and site. Binary outcomes (e.g., complete closure) will be assessed with logistic regression; time-to-event data (e.g., time to 100% closure) with Cox proportional hazards models; and repeated measures with linear mixed-effects models. The significance level is set at *α* = 0.05 (two-sided). Confidence intervals will be reported at 95%. All statistical analyses will be performed using Stata (version 16.1) and R (version 4.3.2).

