### Eligibility criteria

Inclusion criteria require that participants are aged 18 years or older, have a clinical diagnosis of VLU or VLU + PAD, and present with an ankle-brachial index (ABI) between 0.5 and 1.3 or an ankle artery pressure above 60 mmHg. Eligible ulcers must measure between 2 and 50 cm^2^ after debridement at screening and have been present for more than 30 days but less than 2 years. For patients with diabetes, the glycated hemoglobin (HbA1c) must be ≤ 12% at screening. All participants must provide written informed consent prior to any trial-specific procedure.

Exclusion criteria include pregnancy or lactation, active malignancy within the ulcer region, use of photosensitizing medication within the past 30 days, severe immunosuppression (including chronic corticosteroid therapy at > 10 mg/day prednisolone equivalent), New York Heart Association (NYHA) class III or IV heart failure, end-stage renal disease requiring dialysis, ulcer area reduction greater than 30% during the run-in phase, active infection requiring systemic antibiotics at baseline, use of advanced wound therapies (e.g., negative pressure wound therapy, skin substitutes, or hyperbaric oxygen therapy) within 2 weeks before screening, or participation in another interventional clinical trial within the past 30 days.

Eligibility criteria for study staff: Only investigators with experience in wound management and trained in COMS device use perform the intervention.

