## Interventions

### Run-in phase

A 2-week run-in period precedes randomization (see Fig. 1). During this phase, all participants receive optimized SOC, including wound cleansing, appropriate dressings, debridement when indicated, and compression therapy according to international guidelines. Wound area measurements are taken at screening and at the end of the run-in period. Participants whose ulcer area decreases by more than 30% during this period are excluded from randomization, as such wounds are likely to heal adequately with SOC alone. This strategy enriches the trial population with chronic ulcers and increases the study’s power to detect a true treatment effect.

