## Discussion

This study is designed to rigorously assess the efficacy of COMS as an adjunct to SOC in venous and mixed-etiology leg ulcers. These conditions represent a substantial and persistent challenge in wound management, with high prevalence, prolonged healing times, and frequent recurrences, all of which translate into a significant personal and societal burden [3]. Even with optimal SOC, including compression therapy, a substantial proportion of ulcers remain unhealed for extended periods, and recurrence is common within months of closure [28, 29].

One of the distinctive features of the NAZARÉ trial is the incorporation of a 2-week run-in phase prior to randomization. This methodological choice is based on evidence that early healing trajectories can predict eventual outcomes, and that wounds demonstrating rapid healing under SOC alone are less likely to benefit from additional interventions. By excluding ulcers that reduce in size by more than 30% during the run-in period, the study enriches its population for chronic ulcers, thereby improving statistical efficiency and increasing the likelihood of detecting a true treatment effect. This design also reduces heterogeneity in the study population, which is especially important in multicenter, international trials.

The pragmatic elements of the trial, such as allowing SOC to be delivered within harmonized but flexible guidelines and conducting the study in diverse clinical settings, enhance external validity. This approach ensures that the results, if positive, are generalizable to real-world practice across healthcare systems with varying resources and workflows. However, pragmatism also comes with trade-offs, including the inability to fully standardize all aspects of care and the potential for performance bias due to the absence of blinding among patients and treating clinicians.

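### The primary ANCOVA does not adjust for run-in area change, which is measured before randomisation and which the protocol treats as predictive; the cost is a modest loss of precision

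*Protocol article*

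**What the plan says.** The section on statistical methods for primary and secondary outcomes states: "The primary endpoint (PWAR at week 12) will be analyzed using analysis of covariance (ANCOVA) adjusting for baseline ulcer area, ulcer type, and site". The list is given without any opening for further covariates.

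The Run-in phase section says: "Wound area measurements are taken at screening and at the end of the run-in period". It then applies the result as an exclusion rule: "Participants whose ulcer area decreases by more than 30% during this period are excluded from randomization".

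The Discussion gives the reason for the run-in in these terms: "early healing trajectories can predict eventual outcomes, and that wounds demonstrating rapid healing under SOC alone are less likely to benefit from additional interventions".

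On ulcer duration, the Eligibility criteria require that ulcers "have been present for more than 30 days but less than 2 years", and the data collection section says: "Baseline variables (comorbidities, medications, ulcer history) will be collected through structured case report forms".

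Randomisation is stratified by site only (Assignment of interventions: allocation). The sample size rests on an unadjusted two-sample calculation (Sample size).

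**The concern.** The protocol rests a design feature on the claim that the early trajectory foretells the outcome, and measures that trajectory before randomisation in everyone. Its primary model then treats all randomised ulcers alike on this variable: one that grew during the run-in, one that did not change and one that shrank by 25% are not distinguished. Baseline area cannot stand in for the missing term, because two ulcers of equal size at week 0 may have reached it from opposite directions.

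A baseline covariate that predicts the outcome reduces residual variance and so narrows the confidence interval for the treatment effect. It also corrects for chance imbalance, and stratification by site does nothing to balance early healing. Participants and clinicians are unblinded, so readers may ask whether the arms were healing equally before treatment. A prespecified adjustment answers that question; one added after the results are known would be open to challenge.

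**Working it through.** **Inputs.** From the Sample size section: difference 20 points (65% against 45%), SD 33, two-sided alpha 0.05, 90% power, 5% attrition, 61 per arm. From Study setting: ten sites. Assumed, because the documents do not give it: the incremental R² of run-in change, after area, type and site and among those who pass the 30% rule. I also take 33 as the residual SD of the planned model.

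**1. The stated sample size.** Normal approximation: n = 2(1.960 + 1.282)² × 33² / 20² = 57.2, so 58 per arm. Then 58 × 1.05 = 60.9, so 61 per arm and 122 in total. The exact t version gives 58.19 per arm; 58.19 × 1.05 = 61.1 per arm, or 122.2 in total. The stated figure is reproduced without any covariate.

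**2. The planned model.** SE = 33 × √(2/58) = 6.13 points. The covariates use 9 (site) + 1 (area) + 1 (type) = 11 degrees of freedom. Noncentral-t power with 58 evaluable per arm is 89.9%.

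**3. Run-in change added.** Residual SD = 33 × √(1 − R²); SE = residual SD × √(2/58); covariate degrees of freedom 12, leaving 114 − 12 = 102.

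| Incremental R² (assumed) | Residual SD | SE (points) | 95% CI half-width | Power |
|---|---|---|---|---|
| 0 | 33.0 | 6.13 | 12.2 | 89.8% |
| 0.05 | 32.2 | 5.97 | 11.8 | 91.3% |
| 0.10 | 31.3 | 5.81 | 11.5 | 92.6% |
| 0.20 | 29.5 | 5.48 | 10.9 | 95.1% |

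**4. The price if the covariate is useless.** The lost degree of freedom costs less than 0.1 point of power. Chance imbalance in one extra covariate also inflates the variance by about 1/101, or 1%. With both counted, power at R² = 0 is 89.6%, a loss of about 0.3 points. On the same basis the gains above become 91.0%, 92.4% and 94.9%, and the break-even R² is about 0.01.

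**5. What the 30% cut-off leaves.** Excluding fast healers narrows the covariate. Suppose run-in reduction is normal before exclusion, with mean 10, 15 or 20% and SD 25, or mean 10% and SD 40 (illustrative values). Truncation at 30% leaves a fraction v of 0.46 to 0.57 of its variance. With correlation r before truncation, R² afterwards = r²v / (r²v + 1 − r²).

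| r before truncation | R² before | R² after |
|---|---|---|
| 0.3 | 0.09 | 0.04 to 0.05 |
| 0.4 | 0.16 | 0.08 to 0.10 |
| 0.5 | 0.25 | 0.13 to 0.16 |
| 0.6 | 0.36 | 0.21 to 0.24 |

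For r of 0.3 to 0.5 the result lies within or just below the range in step 3.

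**The case against.** The strongest reply is that nothing in the model is wrong. It adjusts for the stratification factor, for baseline area and for aetiology. Under randomisation it gives a valid comparison with or without further covariates, and the power claim does not lean on the missing one. All of that stands. What remains is that the article fixes a closed list and leaves out the one variable on which it founds its run-in.

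A second reply is that the gain is speculative. That is also fair. The relevant quantity is the partial correlation after the existing covariates, and the Discussion's argument is mainly about rapid healers, who are excluded. The covariate is noisy too: it spans two weeks, with debridement allowed during them. Week-0 area is both the end point of run-in change and the denominator of PWAR. If it is measured too large, run-in reduction looks smaller and PWAR looks larger, which weakens the expected positive correlation. These points argue for the lower part of the range, but the break-even R² is only about 0.01.

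A third concerns chance imbalance. A difference of 0.25 SD between arms has probability about 17% at 61 per arm (standard error √(2/61) = 0.181). At an assumed r of 0.4 it would move an estimate not adjusted for run-in change by 0.25 × 0.4 × 33 = 3.3 points. That is about half of one standard error, and the standard error already allows for it. It is not bias.

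Two further inferences are tempting and are not supported. A reader might conclude that ulcer duration is equally an omitted prognostic factor. The protocol uses duration only as an eligibility window; the factors that it says influence healing are a list of comorbidities without duration. A reader might also conclude that baseline area, ranging from 2 to 50 cm², enters untransformed. The article does not state the scale, and that detail can properly sit in the analysis plan.

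**Conclusion.** The point holds as a minor, avoidable loss of precision. Run-in change should be available for every randomised participant, the protocol calls the early trajectory predictive, and the primary model does not use it. Under an assumed incremental R² of 0.05 to 0.20, adjusting for it would add about 1 to 5 points of power and cut the standard error by about 3% to 11% (5.97/6.13 and 5.48/6.13). The worst case is a loss of about 0.3 points of power. The size rests wholly on that assumed R² and on taking 33 as the current residual SD.

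A reader might infer that the primary analysis is biased or the trial underpowered. Neither follows: the ANCOVA is valid as written, and 122 participants give the stated 90% power without this covariate.

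**What to change.** In the section on statistical methods for primary and secondary outcomes, extend the covariate list to: baseline ulcer area, percentage area change from screening to week 0 (continuous), ulcer type and site. Carry the same wording into the analysis plan. Ulcer duration may be added on clinical grounds, but it is optional and the case for it has to be made separately.

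Make the change before any unmasking. The article says that analyses use masked codes until database lock, and that recruitment began in October 2025 with completion expected in December 2027, so there is time. No new data and no change in sample size are needed. The statistical cost is one degree of freedom. The administrative cost is more than an edited sentence: the section on communicating amendments names changes in statistical methods among substantial amendments, so ethics committees, the registry and all investigators must be told.

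### The primary ANCOVA omits run-in area change, a pre-randomisation value that the protocol itself calls predictive; adding it is a cheap gain in precision, not the repair of an error

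*Protocol article*

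**What the plan says.** Under *Statistical methods for primary and secondary outcomes*, PWAR at week 12 is to be "analyzed using analysis of covariance (ANCOVA) adjusting for baseline ulcer area, ulcer type, and site". The list is closed: three covariates, none of which describes how the ulcer behaved before randomisation.

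Under *Run-in phase*, all participants receive standard of care for two weeks, and "Wound area measurements are taken at screening and at the end of the run-in period". The result is used once: "Participants whose ulcer area decreases by more than 30% during this period are excluded from randomization". The *Visit schedule* places screening at week −2 and randomisation at week 0, so both measurements precede allocation.

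The *Discussion* bases the run-in on evidence that "early healing trajectories can predict eventual outcomes", and presents the exclusion as a way to improve statistical efficiency.

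Under *Sample size*, "A total of 122 participants (61 per group) will provide 90% power to detect a 20% absolute difference", with an SD of 33%, two-sided alpha of 0.05 and 5% attrition. The calculation used R's power.t.test, which takes no credit for any covariate.

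**The concern.** The design and the analysis treat the same variable differently. The design holds that early trajectory carries prognostic information, and spends two weeks per patient collecting it. The primary model then keeps only which side of 30% the ulcer fell on, and among those randomised everyone is on the same side.

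An ulcer that shrank by 29% in the run-in and one that grew enter the model identically if they share week-0 area, type and site. Week-0 area does not stand in for trajectory: two ulcers of 10 cm² at randomisation can have reached that size from opposite directions.

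Two things are at stake. Outcome variance that trajectory could explain stays in the error term. And a chance imbalance in healing rate between arms is not adjusted for, because randomisation is stratified by site only.

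**Working it through.** **Inputs from the protocol.** Difference 20 points, SD 33, two-sided alpha 0.05, power 90%, 61 per arm, 5% attrition (*Sample size*); ten sites (*Study setting*); 1:1 allocation.

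**Input that is assumed.** The partial correlation *r* between run-in change and week-12 PWAR, given the planned covariates. The documents give no value, so a range of 0.2 to 0.4 is used.

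**Step 1: reproduce the plan's figure.** Normal approximation: n = 2 × [33 × (1.960 + 1.282) / 20]² = 57.2, so 58 per arm. Attrition: 58 × 1.05 = 60.9, or 58 / 0.95 = 61.05, both about 61. The stated 122 reproduces. In the other direction, 61 × 0.95 = 57.95, so about 58 are analysed per arm. Power with 58 per arm is 90.4% (normal) or 89.9% (t-test), with no covariate involved.

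**Step 2: cost of one more covariate.** With 116 analysed, the planned model leaves 116 − 1 (intercept) − 1 (treatment) − 1 (area) − 1 (type) − 9 (site) = 103 residual degrees of freedom. One more covariate leaves 102 and inflates the variance of the treatment effect by about 1 + 1/101, or 1%. Break-even is therefore at r² of about 0.01, or r of about 0.1.

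**Step 3: gain.** SE = 33 × √(1 − r²) × √(2/58) × √(1 + 1/101). Here 33 is treated as the residual SD after the planned covariates. The last factor applies only when the covariate is added. Power is from the noncentral t with 102 degrees of freedom.

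| r | r² | SE (points) | 95% CI half-width (1.96 × SE) | Power | Equivalent extra participants |
|---|---|---|---|---|---|
| not added | – | 6.13 | 12.0 | about 90% | – |
| 0.2 | 0.04 | 6.03 | 11.8 | 90.7% | 3% |
| 0.3 | 0.09 | 5.87 | 11.5 | 92.1% | 9% |
| 0.4 | 0.16 | 5.64 | 11.1 | 93.9% | 18% |

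The last column is 1 / [(1 − r²) × (1 + 1/101)] − 1.

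**Step 4: effect of the 30% exclusion.** Removing ulcers that shrink by more than 30% truncates the covariate. Assume percentage reduction in the run-in is roughly normal, with mean 10–20 and SD 20 or mean 15 and SD 30. The fraction *v* of its variance left after truncation is then about 0.49 to 0.63. An untruncated correlation ρ becomes R² = ρ²v / (ρ²v + 1 − ρ²):

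- ρ = 0.3 gives R² of about 0.05–0.06
- ρ = 0.4 gives about 0.09–0.11
- ρ = 0.5 gives about 0.14–0.17

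Taking square roots, these correspond to correlations of about 0.2 to 0.4. The range in step 3 thus already matches what truncation would leave of untruncated correlations of 0.3 to 0.5.

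**The case against.** The strongest reply is that this is a preference and not a defect. Under randomisation, omitting a prognostic covariate neither biases the estimate nor invalidates the test. The model contains site, the only stratification factor, and baseline area. The stated power takes no credit for covariates and is met without this one. All of that stands, and it rules out a reading that the primary analysis is wrong or underpowered.

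The reply also notes that the gain rests on an assumed correlation, that the covariate is not free, and that truncation weakens it. Those points stand too, and they are why the gain is modest. In addition, if the planned covariates already explain part of the variance, power starts higher and fewer points remain to be gained.

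The reply does not remove the mismatch. The covariate list is a stated choice and not a silence left to an analysis plan, and the protocol itself calls the omitted variable predictive.

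A reader might be tempted further on three matters, and the document does not support any of them:

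- *Ulcer duration as a second omitted covariate that the protocol regards as prognostic.* Duration appears only as an eligibility window: ulcers must "have been present for more than 30 days but less than 2 years". The variables collected "as these are known to influence ulcer healing trajectories" are a list of comorbidities, and duration is not among them.
- *Baseline area should be log-transformed.* Functional form is a detail that a condensed article may leave to the analysis plan.
- *The logistic, Cox and mixed models ignore the site strata.* The article names these model families without giving their covariates. That does not say they are unadjusted.

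**Conclusion.** The point holds as an efficiency improvement limited to one covariate in the primary model. Run-in area change is available on everyone before randomisation, the protocol relies on its predictive value, and the primary ANCOVA does not use it.

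At 58 analysed per arm, adding it moves power from about 90% to about 91–94% and narrows the 95% CI half-width from 12.0 to between 11.8 and 11.1 points. This assumes a partial correlation of 0.2 to 0.4 and a residual SD of 33, and it charges one degree of freedom. Below a correlation of about 0.1 there would be no gain. The 30% exclusion makes the upper part of the range less likely than it would be in an unselected population.

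The planned analysis remains valid and the sample-size claim is unaffected.

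**What to change.** Before treatment codes are unmasked at database lock, pre-specify one further covariate in the primary ANCOVA: percentage area change from week −2 to week 0. Screening area entered alongside baseline area would be an acceptable alternative. Choose one form and fix it in advance.

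The cost is one of about 103 residual degrees of freedom and a wording change. No new data are needed, because both measurements are already taken. The section on communicating amendments counts changes in statistical methods as substantial, so the change should be notified by that route. *Trial status* gives recruitment from October 2025 to an expected completion in December 2027, which leaves time to do so.
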